
# 4. Statistical Analysis Plan

The INtravenous CLArithromycin in Sepsis with multiple organ dysfunction Syndrome (INCLASS) study aims to assess the efficacy of clarithromycin as adjunctive treatment in reducing all-cause 28-day mortality among severely ill patients with sepsis. The study also aims to provide insight on the mechanism of action underlying clinical outcomes. The study statistical analysis plan (SAP) was conducted by the protocol authors ([name] and [name]), as well as the study statistician [name]. [name] provided statistical advice on bioinformatics for RNA sequencing. The SAP was established on 26/06/2019, at the end of enrollment and before the unmasking, the database lock and the end of the follow-up period.

**Study Design**

The INCLASS study is a multicenter, international, placebo-controlled, double-blind, parallel group Randomized Clinical Trial (RCT). It is hypothesized that intravenous clarithromycin, as adjunctive treatment to standard of care for sepsis reduces all-cause 28-day mortality compared to placebo. The study aims to include 110 patients from 13 investigational sites, ICU and non-ICU, in Greece and in Belgium.

**Randomization and bliniding**

Patients are assigned to clarithromycin or placebo, following a random allocation sequence, with a 1:1 design and by block sizes of 10, stratified per study site. The allocation sequence was generated by an independent statistician prior to the study start and delivered within sealed individual envelopes, labeled per study participant code, to each study site. The envelope is unsealed by the study pharmacist (the only unblinded investigator), to prepare the study drug. All other parties involved (investigators, patients, healthcare providers) are blinded to the study arm.

Study intervention consists in either 1gr of clarithromycin or 20 ml of water for injection (placebo), administered once daily as a ready-to use intravenous solution of 250 ml D/W 5%. The intervention is administered for 4 consecutive days, as soon as possible after enrollment. There is no specific time window from enrollment to study drug administration, which is required to be as soon as logistically possible.

**Study Population**

**Inclusion Criteria**

- Adult patients (≥18 years)
- Patients of both genders
- Informed consent form signed by patient or by first-degree relative in case of patient unable to consent
- Negative (blood or urinary) pregnancy test for female patients of reproductive age
- Willingness to receive contraception during and seven days after the administration of the study drug.
- Presence of one or more of the following infections: hospital-acquired pneumonia (HAP), health-care associated pneumonia (HCAP), ventilator-associated pneumonia (VAP), primary Gram-negative bacteremia or intra-abdominal infections. Definitions for these infections are given below.
- Presence of sepsis as defined by the Sepsis-3 classification criteria^3^ (see definitions section below)
- Respiratory dysfunction defined as one PaO_2_/FiO_2_ ratio inferior to 200, independently of the PEEP level.
- Total sequential organ failure assessment (SOFA) score for organ dysfunctions other than respiratory system more than 3

***Exclusion criteria***

Patients who meet ANY of the exclusion criteria below cannot be enrolled in the study:

- Denial for informed consent
- Age inferior to 18 years
- Pregnancy (confirmed by blood or urinary pregnancy test) or lactation for female patients of reproductive age.
- Unwillingness to receive contraception during and seven days after the administration of the study drug.
- HIV infection (with known CD4 cell count ≤ 200/mm^3^)
- Solid organ, or bone marrow transplantation
- Corticosteroid oral or intravenous intake greater than 0.4 mg/kg of equivalent prednisone daily over the last 15 days; anti-cytokine biological agents (e.g. anti-TNFα), anti-lymphocyte immunoglobulins, Mycofenolate Mofetil, Tacrolimus (FK506) and m-TOR inhibitors (any dose of the above within the past 3 months); Chemotherapy within the past 3 months, Leflunomide intake within the past 2 year, Rituximab within the last year; Methotrexate, Azathioprine, Cyclosporine, Cyclophosphamide (any dose of the above within the last 3 months). Splenectomy, known primary immunodeficiencies. Hydroxyurea, anti-Vascular Endothelial Growth Factor (VEGF), anti-Epithelial Growth Factor Receptor (EGFR), anti-Growth Factor Her-2 and Interferon a, b and γ intake are not considered as exclusion criteria.
- Known active neoplasms or other medical conditions unrelated to sepsis (any of the two), that are compromising short-term survival (1 month)
- Neutropenia <1000/mm^3^
- Known allergy to macrolides
- Previous participation in the study
- Administration of a macrolide for the current infectious episode

**Primary study endpoint**

All-cause 28-day mortality.

**Secondary study endpoints**

- 28-day mortality in the subgroup of patients with septic shock
- All-cause 90-day mortality
- Early sepsis response, defined by an at least 25% decrease of day 1 SOFA score on day 3
- Sepsis resolution; this is defined by an at least 25% decrease of day 1 SOFA score on day 7
- New sepsis episode until day 28. A new sepsis episode is defined as a further increase of SOFA score by at least 2 points consequent to infection, in a patient who has experienced previous sepsis resolution (at least 25% decrease of day 1 SOFA score on day 7)
- Time until new sepsis episode. A new sepsis episode is noted in any patient who experiences any more than 25% decrease of day 1 SOFA score on day 7 and who has further increase of SOFA by at least 2 points, consequent to infection
- Biomarkers of host immune response, through genome, metabolome, transcriptome, microbiome and cell population analysis
- The (primary) health economic outcome is cost per quality-adjusted life-year (QALY) gained for clarithromycin compared with placebo.

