| Resolution/ recurrence of infection** |  |  |  |  |  |  | x | x | x | x | x | x | x | x | x | x | x | x | x | x | x | x | x | x | x | x | x | x |  | |
| AE monitoring | x | x | x | x | x | x | x | x | x | x |  |  |  |  |  |  |  |  |  |  |  |  |  |  |  |  |  |  |  | |
| Microbiology** | x | x | x | x | x | x | x | x | x | x | x | x | x | x | x | x | x | x | x | x | x | x | x | x | x | x | x | x |  | |
| Pregnancy test*** | x |  |  |  |  |  |  |  |  |  |  |  |  |  |  |  |  |  |  |  |  |  |  |  |  |  |  |  |  | |
| PAX Gene | x |  |  |  | x |  |  |  |  |  |  |  |  |  |  |  |  |  |  |  |  |  |  |  |  |  |  |  |  | |
| Serum metabolomics | x |  |  |  | x |  |  |  |  | x |  |  |  |  |  |  |  |  |  |  |  |  |  |  |  |  |  |  |  | |
| PBMCs isolation | x |  |  |  | x |  |  |  |  | x |  |  |  |  |  |  |  |  |  |  |  |  |  |  |  |  |  |  |  | |
| Stool sample | x |  |  |  | x |  |  |  |  |  |  |  |  |  |  |  |  |  |  |  |  |  |  |  |  |  |  |  |  | |

- * SOFA score: if available according to usual clinical practice. On days where SOFA components are not available (e.g. no blood analysis programed by the physician or discharged patient), the last known value will be recorded.
- ** If available and justified by clinical context ***For female patients of reproductive age

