**Populations**

Analyses will be performed on an intention-to-treat (ITT) basis, including all randomized patients, independently of wheather they received the sudy intervention. The ITT population will enter analysis of the primary and all secondary outcomes. In case of consent withdrawal, all data collected prior to this point will be excluded.

The following subgroups of patients are potentially identified:

- Enrolled inside and outside of the intensive care unit (ICU)
- Enrollement in Greece and in Belgium
- Presence or absence of septic shock
- Presence or absence of acute respiratory dysfunction syndrome (ARDS)
- Extremely high severity, defined as patients within the highest quartile of SOFA score, vs all others.
- Presenting pneumonia, intra-abdominal infection or primary Gram-negative bacteremia
- Presence or absence of a Gram-negative pathogen (among infections with identified pathogen only)
- Adequate vs non-adequate empirical antimicrobial treatment (among infections with identified pathogen only). Empirical antimicrobial treatment (defined as the regimen given within 48 hours from infection onset, when cultures are pending) is considered as adequate when administered at the indicated dose and with penetration to the infected site; provided that the identified pathogen has documented or reasonably suspected susceptibility (e.g. metronidazole for *Clostridioides difficile* infection)
- Per protocol (PP) population, defined by patients receiving the entire intervention (all 4 daily doses)

Subgroup analyses will be performed for mortality outcomes (28-day and 90-day).

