**Analyses for secondary outcomes**

The effect of the study arm on secondary outcomes will be compared with the Pearson chi-square test, or the two-sided Fisher’s exact test for 90-day mortality, early sepsis response and sepsis resolution, as well as new sepsis incidence. Clinical secondary outcomes will be evaluated on an ITT basis.

- Regarding 90-day mortality, the following subgroup analyses are planned (for all subpopulations identified): per country; per ward of enrollment (ICU or general ward); per protocol (according to whether the study intervention was complete -all 4 doses received); per presence of septic shock (already present in the protocol); per highest SOFA score (defined as higher or lower than the upper SOFA quartile of the population); per presence of ARDS; per initial infectious site; per adequacy of empirical antimicrobial treatment; and per Gram-negative vs non-Gram negative pathogen, among infections with identified pathogens. Interactions between subgroups and arm of treatment were assessed with Breslow-Day test and confirmed with logistic regression for the primary outcome.
- The time to new sepsis incidence will be compared only for patients experiencing a new sepsis episode both by the Mann-Whitney test, and as Cox-regression analysis of the treatment effect on the time to new sepsis episode, with death as competing event.
- Cell populations and monocytic HLA-DR variables will be assessed using Student’s t-test (for variables following a normal distribution), Mann-Whitney U (for variables following a skewed distribution), as appropriate. Overtime changes will be assessed by the k-related samples non-parametric Friedman test, separately per study arm, and the mixed ANOVA test with time and study arm as within-subject and between-subject factors respectively.
- Transcriptomic data wil be illustrated by Volcano plots for differential expression of genes among study groups, while gene set enrichement analysis will also be performed to identify pathways of transcriptomic changes among study groups. Any need for additional (post-hoc) analyses will be re-evaluated. Functionality of differentially expressed transcripts will be assessed by the ENCODE project.

Raw sequence data and count data will be uploaded on National Center for Biotechnology Information (NCBI) gene expression omnibus (GEO), to be publicly available.

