**Missing values**

Missing values will be treated as such, and the number and percentage of patients or events entering each step of the analysis will be provided. The Little’s test will be used to assess whether missing values are missing completely at random.

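### The plan does not say how patients who die before day 3 or day 7 are classified for early sepsis response and sepsis resolution, and its two rules for an absent SOFA give different answers

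*Supplement*

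**What the plan says.** The SAP (Secondary study endpoints) lists "Early sepsis response, defined by an at least 25% decrease of day 1 SOFA score on day 3" and "Sepsis resolution; this is defined by an at least 25% decrease of day 1 SOFA score on day 7". The final protocol uses the same definitions. Both endpoints are binary and need a score on a fixed day. The SAP (Analyses for secondary outcomes) compares them by Pearson chi-square or Fisher's exact test.

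On who is analysed, the SAP (Populations) states: "The ITT population will enter analysis of the primary and all secondary outcomes". Analyses for secondary outcomes adds: "Clinical secondary outcomes will be evaluated on an ITT basis".

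On an absent score there are two rules:

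- SAP, Missing values section: "Missing values will be treated as such, and the number and percentage of patients or events entering each step of the analysis will be provided". Little's test is planned, but nothing follows from its result.
- Final protocol, Appendix V, footnote to the SOFA row, for days when "SOFA components are not available (e.g. no blood analysis programed by the physician or discharged patient), the last known value will be recorded".

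Neither rule mentions death. Elsewhere the authors do give death a place: it scores 0 on the quality-of-life scale (protocol, Cost-Effectiveness analysis) and is a competing event for time to new sepsis (SAP, Analyses for secondary outcomes).

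**The concern.** A patient who dies on day 2 has no day 3 score, and one who dies on day 5 has no day 7 score. Two analysts following the documents could classify that second patient differently, and both could point to a written rule.

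This matters because death is the outcome the drug is meant to change. If clarithromycin lowers mortality as planned, a day 7 score will be absent more often on placebo, and absent because of the outcome. A table of survivors then no longer compares the groups as randomised, and any gain from keeping patients alive to day 7 disappears from the endpoint. Carrying the last score forward keeps everyone in the table but can credit some deaths as successes. Unless the choice is fixed before unmasking, it can be made with the results in view.

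**Working it through.** **1. The rules applied to one patient.** Take a day 1 SOFA of 12, a last score before death of 9, and death on day 5. The fall is (12 − 9)/12 = 25%.

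- Left missing (SAP, Missing values): the patient leaves the 2×2 table.
- Last known value (protocol, Appendix V): the patient counts as resolved on day 7.
- All randomised patients analysed, with a dead patient having no decrease on day 7 (one reading of the ITT statements): the patient counts as not resolved.

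The documents thus allow three outcomes for one patient, and the SAP does not say which rule takes precedence.

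**2. The plan's own figures.** No sample size or power is tied to the SOFA endpoints, so there is no figure for them to reproduce. The planning inputs come from the protocol's Power calculation: 55% versus 30% mortality, type I error 0.10, power 0.8. The two-proportion formula with two-sided alpha 0.10 gives 48 per arm without continuity correction and 55 with it, which matches the stated 55. These rates imply 55 × 0.55 = 30.25 and 55 × 0.30 = 16.5 deaths by day 28.

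**3. Size of the effect on day 7 resolution.** The following are assumptions, because the documents give no day 3 or day 7 mortality and no response rate:

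- *f*, the share of 28-day deaths that fall before day 7, is the same in both arms: 25%, 50% or 60%.
- *r*, response among day 7 survivors, is 60% in both arms.
- *q*, the share of early deaths whose last SOFA was already at least 25% below day 1, is 0 to 20%.

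With early mortality *d* = *f* × 0.55 (placebo) or *f* × 0.30 (clarithromycin):

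- Survivors only: rate = *r* in each arm, so the difference is 0.
- Death as non-response: rate = (1 − *d*) × *r*, so the difference is *r* × *f* × 0.25.
- Last value carried forward: rate = (1 − *d*) × *r* + *d* × *q*, so the difference is (*r* − *q*) × *f* × 0.25.

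| *f* | Early mortality, placebo / clarithromycin | Survivors of 55 | Survivors only | Death as non-response | Carried forward, *q* = 20% |
|---|---|---|---|---|---|
| 25% | 13.75% / 7.5% | 47.4 / 50.9 | 60% / 60%, diff. 0 | 51.75% / 55.5%, diff. 3.75 | 54.5% / 57.0%, diff. 2.5 |
| 50% | 27.5% / 15% | 39.9 / 46.8 | 60% / 60%, diff. 0 | 43.5% / 51.0%, diff. 7.5 | 49.0% / 54.0%, diff. 5.0 |
| 60% | 33% / 18% | 36.9 / 45.1 | 60% / 60%, diff. 0 | 40.2% / 49.2%, diff. 9.0 | 46.8% / 52.8%, diff. 6.0 |

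At *q* = 0, carrying forward gives the same result as death as non-response. In the middle row with *q* = 20%, 55 × 0.275 × 0.2 = 3.0 placebo and 55 × 0.15 × 0.2 = 1.7 clarithromycin deaths would be counted as resolved.

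**4. Sensitivity.** With *r* = 50% and *f* = 50%, death as non-response gives 0.5 × 0.5 × 0.25 = 6.25 points. If early mortality and *q* are equal in the two arms, and survivors respond equally, all three rules give a difference of 0, although the rate within each arm still depends on the rule. For day 3 the formulas are the same. Deaths by day 3 cannot exceed deaths by day 7, so at the same *r* the shift is no larger.

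**The case against.** The strongest reply is that the plan already contains the answer. All randomised patients enter every secondary outcome, and a dead patient shows no SOFA decrease on day 7, so death is non-response. That reading is open and sensible. It is not written down, however, and it has to be reconciled with a missing-values rule that makes no exception for death.

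A reader might infer that the plan drops the dead, or that it carries their scores forward. The documents say neither. The SAP does not state that a death makes the SOFA a missing value. The footnote's examples are a day without blood tests and a discharged patient; the list is open, but death is not on it. Even if the footnote were applied, SOFA is scheduled daily, so the value carried would be the last before death. It would produce a false resolution only if it was still at least 25% below day 1. A patient who died with only the day 1 score recorded would be a non-responder.

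A reader might also extend the point to new sepsis episodes, since these require prior resolution on day 7. That does not follow: a patient dead by day 7 cannot have a later episode, so the count of episodes is the same under every rule, and for time to new sepsis death is already a competing event.

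Three mitigating facts stand. The SAP (General principles) treats all secondary outcomes as exploratory. The numbers entering each analysis will be reported, so excluded deaths would be visible. Survival status is recorded daily, so the table could be recomputed.

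**Conclusion.** The point holds as a gap in the definition of two secondary endpoints. The documents do not classify deaths before day 3 or day 7. Of the two written rules for an absent SOFA, one would give a survivor-only comparison that conflicts with the ITT statements, the other could count a death as resolution, and they disagree with each other. It should not be read as a finding that the plan prescribes either treatment of deaths.

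Relative to a survivor-only table, counting death as non-response moves the day 7 difference by roughly 4 to 9 points. That rests on the planning mortality of 55% versus 30%, and on assuming 25–60% of deaths before day 7 and 60% response among survivors in both arms. The documents support only the mortality figures, so the range shows how far the choice could matter and does not estimate what happened. It would shrink towards zero if early mortality were similar in the two arms.

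The ambiguity should be fixed, but it is not critical to the trial. The primary endpoint, 90-day mortality and the sample size are unaffected.

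**What to change.** Add two sentences to the SAP under Secondary study endpoints. First, early sepsis response and sepsis resolution are evaluated in all randomised patients, and a responder is a patient alive on the assessment day whose SOFA is at least 25% below day 1; death on or before that day is non-response. Second, the last known SOFA is carried forward only for a patient known to be alive on that day. Cross-refer to both from Missing values and from the Appendix V footnote, so that one rule governs.

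No new data are needed, because survival status is already recorded daily to day 28. The SAP states that it was established before unmasking and database lock, and that was the time to settle the rule at no cost. A survivor-only table may be shown beside the main one if it is labelled as descriptive.

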**Safety outcomes**

- Adverse events (AEs)
- Serious adverse events (SAEs)
- Suspected unexpected serious adverse reactions (SUSARs)

Patients are followed-up daily until day 28 or hospital discharge (whatever comes first). In case of earlier discharge, the primary outcome, is assessed by phone call at day 28. 90-day mortality and quality of life by the EuroQol**^®^** 5-dimension 3-level (EQ-5D-3L) questionnaire (1), in case of discharge, are also assessed by phone call with the patient or their caregiver. Safety outomes are captured daily until day 28 or discharge (whichever comes first) and as patient or provider-reported events until day 90. All other secondary outcomes are assessed until day 28 or discharge.

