***Study visits***

*Screening visit*

When a patient meets ALL inclusion criteria and NONE of the exclusion criteria, he/she can be enrolled in the study. The criteria are judged based on data available from the patient’s file. Female patients of reproductive age should be screened with a urinary pregnancy test. QT prolongation or prior arrhythmia is not considered as an exclusion criterion for the study, ^9,11^ but may be considered in the decision making of the principal investigator. The same patient cannot be enrolled twice in this study.

*Patient follow-up*

Follow-up of every patient will be done daily until day 28 or hospital discharge (whatever comes first).

Visit 1 is on day 1. Procedures of this day include:

- Recording of demographics, medical history, co-morbidities (Charlson Comorbidity Index), ^17^ SOFA score (see APPENDIX II); Acute Physiology and Chronic Health Evaluation (APACHE) II score (see APPENDIX III), available blood cell count, biochemistry, coagulation time, urine output, blood gas analysis, recording of suspected infection site, available radiological findings, relevant for the current infection microbiology and antimicrobial susceptibility testing if available, administered antimicrobials, other administered drugs and need for source infection control either by percutaneous interventions or by any operation.
- Sampling of 35 ml of venous blood; 3ml is collected into one PAXgene tube or a tube with RNA*later*®; 9ml is collected into one pyrogen-free tube; and 24ml is collected into EDTA-coated tubes
- Collection of stool culture or rectal swab
- Administration of the study drug
- Evaluation of potential adverse events

Visit 2 is on day 2. Procedures of this day include:

- Recording of SOFA score (see APPENDIX II); available blood cell count, biochemistry, coagulation times, urine output, blood gas analysis, available radiological findings, relevant for the current infection microbiology and antimicrobial susceptibility testing if available, administered antimicrobials, other administered drugs and need for source infection control either by percutaneous interventions or by any operation.
- Survival status
- Administration of the study drug
- Evaluation of potential adverse events

Visit 3 is on day 3. Procedures of this day include:

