- Evaluation of resolution of the infection and potential recurrence of infection according to the judgment of the attending physician
- Evaluation of potential adverse events

Visit 10 is on day 10. Procedures of this day include:

- Recording of SOFA score (see APPENDIX II); available blood cell count, biochemistry, coagulation times, urine output, blood gases, available radiological findings, clinically relevant microbiology and antimicrobial susceptibility testing, administered antimicrobials, other administered drugs and need for source infection control either by percutaneous interventions or by any operation.
- Survival status
- Evaluation of resolution of the infection and potential recurrence of infection according to the attending physician
- Sampling of 33 ml of venous blood; 9ml is collected into one pyrogen-free tube; and 24ml is collected into EDTA-coated tubes
- Evaluation of potential adverse events

Visits 11-28 are on days 11-28 respectively. They include

- Recording of SOFA score if available
- Administered antimicrobials, other administered drugs and need for source infection control either by percutaneous interventions or by any operation.
- Survival status
- Evaluation of resolution of the infection and potential infection recurrence according to the judgment of the attending physician
- Evaluation of potential adverse events

If the patient is discharged before day 28, a phone call will be performed on day 28 to assess survival status, need for new hospitalization or antibiotic therapy and potential adverse events. End-of-life decisions, if any, will be recorded.

Last visit: A phone call follow-up will be done on day 90 to assess survival status. If available, data concerning any new hospitalization, or antibiotic cure and potential adverse events will be collected during that phone call. Moreover, a self or proxy-assessment of health-related quality of life will be performed through the EQ-5D-3L^™^ questionnaire on the same visit (see APPENDIX IV) ^18^.

All information will be recorded on a specific paper Case Report Form (CRF).

The procedure to follow at each study visit is shown in APPENDIX V.

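### New sepsis is defined to day 28 but assessed only to discharge, so episodes after discharge are missed and those patients count as event-free

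*Supplement*

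**What the plan says.** The SAP (Secondary study endpoints) lists "New sepsis episode until day 28" and defines the event as a "further increase of SOFA score by at least 2 points consequent to infection, in a patient who has experienced previous sepsis resolution", where resolution means a SOFA fall of at least 25% from day 1 to day 7. Time until the new episode is a separate endpoint.

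The follow-up paragraph under the SAP's Safety outcomes carries the primary outcome, 90-day mortality, quality of life and safety beyond discharge. It then closes: "All other secondary outcomes are assessed until day 28 or discharge". Protocol version 2 (Study visits) agrees: "Follow-up of every patient will be done daily until day 28 or hospital discharge (whatever comes first").

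Under the SAP's Populations section, all randomised patients enter every secondary analysis. Under Analyses for secondary outcomes, new sepsis incidence is tested by Pearson chi-square or Fisher's exact test. Time to new sepsis is compared only among patients who have an episode, by Mann-Whitney and by Cox regression with death as the competing event. Discharge is not mentioned.

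Two protocol provisions bear on the period after discharge. For patients who leave early, "a phone call will be performed on day 28 to assess survival status, need for new hospitalization or antibiotic therapy and potential adverse events". The SOFA footnote to Appendix V covers days without SOFA components and gives discharge as an example; it ends "or discharged patient), the last known value will be recorded".

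**The concern.** The horizon in the endpoint's definition and the period in which it can be observed do not match. A test on a 2x2 table over all randomised patients needs each patient classified as event or no event by day 28. For anyone discharged earlier, the period from discharge to day 28 is unobserved, yet the patient falls into the no-event cell.

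Two consequences follow. If new sepsis occurs after discharge, incidence to day 28 is understated. If the arms also differ in when patients leave, the understatement differs by arm and the comparison mixes recurrence with length of stay. Sepsis recurrence is a named secondary aim in the protocol, and two listed endpoints rest on this event.

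**Working it through.** **1. Can an episode after discharge be counted?** Set the rules side by side.
- Definition: a SOFA rise of at least 2 points due to infection, up to day 28.
- Observation: SOFA visits and endpoint assessment end at discharge.
- Day-28 call: asks about survival, rehospitalisation, antibiotics and adverse events. It yields no SOFA, and neither the definition nor the SAP uses the answers for this endpoint.
- Missing values (SAP): left as missing, but nothing says that a discharged patient is missing for this endpoint.
- Adverse events (protocol): events resulting from sepsis or infection are not recorded as AEs or SAEs because they are endpoints, so safety data need not supply them.
- Time analysis: as worded, it is confined to patients with an episode, so it cannot correct for shorter observation in the others.

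As written, no route exists.

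**2. Inputs for size.** No discharge or recurrence rate is given, so all such rates below are assumptions. The plan's only design figure is 55 patients per arm for mortality. It is reproduced by 55% v 30%, two-sided alpha 0.10, power 0.80 and continuity correction. Only those mortality rates are borrowed here.

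**3. Constant daily risks over the 21 days 8 to 28, continuing after discharge.** Let e, d and m be the daily probabilities of event, discharge and death, and q = (1−e)(1−d)(1−m). Observed incidence = e(1−q²¹)/(1−q), counting an event before an exit on the same day.
- e = 1−0.8^(1/21) = 0.01057 for a true 20%, and 1−0.7^(1/21) = 0.01684 for a true 30%.
- d = 0.02 gives 1−0.98²¹ = 35% discharged; d = 0.04 gives 1−0.96²¹ = 58%.

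With no deaths (m = 0) and a true 20%: q = 0.9696 gives 16.6% (slower discharge), and q = 0.9499 gives 13.9% (faster). With a true 30%: 25.0% v 21.1%. That is a false gap of about 3 to 4 points and an understatement of 17% to 30%.

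**4. Add the plan's mortality.** Give the slower-discharge arm 55% and the faster arm 30%. With all deaths in the window, m = 1−0.45^(1/21) = 0.0373 and 1−0.70^(1/21) = 0.0168. With half of the deaths before the window, 72.5% and 85% enter it, and the death risk within it is 0.275/0.725 = 37.9% and 0.15/0.85 = 17.6%. The last column sets d = 0, so no episode is lost to discharge.

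| Case (slower v faster discharge) | Observed | No loss at discharge |
|---|---|---|
| True 20%, all deaths in window | 12.1% v 12.2% | 14.2% v 17.1% |
| True 30%, all deaths in window | 18.5% v 18.5% | 21.6% v 25.7% |
| True 20%, half of deaths earlier | 9.9% v 11.0% | 11.8% v 15.6% |
| True 30%, half of deaths earlier | 15.0% v 16.7% | 17.7% v 23.4% |

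The gap from step 3 vanishes or reverses. Episodes are still lost: in the first row, 14.2−12.1 = 2.1 points in one arm and 17.1−12.2 = 4.9 in the other. Deaths offset the distortion in the observed comparison but do not remove it.

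**5. A second illustration, without deaths.** In arm A 50% leave on day 14; in arm B 30% leave on day 21. With true risk R, h = −ln(1−R)/21, and observed incidence = share × (1−exp(−h(day−7))) + (1−share) × R. For R = 25%: A = 0.5×9.1% + 0.5×25% = 17.1%; B = 0.3×17.5% + 0.7×25% = 22.7%. For R = 15%: 10.1% v 13.6%. For R = 35%: 24.2% v 32.0%.

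With equal discharge (30% on day 18 in both arms), a true 25% is seen as 21.7% in each: under-counted, with no false difference. If the hazard after discharge is 0, 25, 50 or 100% of the in-hospital hazard, the bias in the difference at R = 25% is 0, −1.5, −3.0 or −5.7 points.

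**The case against.** The strongest reply is that the direction is not established. A reader might infer that the arm with earlier discharge, presumably clarithromycin, will look better. The documents do not support that. Only patients with day-7 resolution can have an event, and the dead are non-events too. Step 4 shows that the plan's own mortality assumption can cancel or reverse the gap. The protocol's Introduction reports earlier weaning and faster resolution of pneumonia with clarithromycin, not shorter hospital stay. This objection stands.

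Second, a reader might infer that carrying SOFA forward is what classifies discharged patients as event-free. The Appendix V footnote is a recording rule, attached to a table that itself runs only to day 28 or discharge. The SAP never says that the carried value determines the endpoint. This also stands: the carry-forward is a risk to close off, and the mismatch exists without it.

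Third, in-hospital new sepsis is a legitimate endpoint, and censoring at discharge in the Cox model would be a natural reading. The first half is right and points to the simplest fix. The second helps less: the SAP does not state it, the comparison is worded as confined to patients with an episode, and censoring at discharge assumes that those who leave keep the same risk as those who stay.

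Fourth, the effect is small for this trial. With 55 per arm and incidence near 20%, the 95% half-width of a difference is 1.96×√(2×0.2×0.8/55) = 15 points, and the SAP treats all secondary outcomes as exploratory. This limits the weight of the point but does not correct the count.

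**Conclusion.** The mismatch is real in the current text. The endpoint claims a day-28 horizon, assessment stops at discharge, and the planned test counts discharged patients as event-free. Neither the day-28 call nor the missing-values rule repairs this.

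Under-counting requires some recurrence after discharge; with none, nothing is lost. Distortion between arms also requires different discharge timing. Under the assumed rates, without deaths, the false gap is about 3 to 8 points. With the plan's mortality rates the observed gap is nil or reversed. These figures are illustrations, and no net direction can be claimed. The matter is worth correcting but not critical: the endpoint is exploratory, and 28-day mortality has its own call at day 28.

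**What to change.** Amend the SAP before unmasking.

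1. Label the main endpoint as in-hospital new sepsis to day 28, report person-days at risk per arm, and state that SOFA carried forward after discharge is not evidence of no event.
2. Estimate cumulative incidence in all eligible patients, not only those with an episode, with death and discharge alive as competing events. Show censoring at discharge only as a sensitivity analysis, because it assumes similar risk afterwards.
3. Add a sensitivity analysis that counts a new hospitalisation with antibiotic therapy, reported at the day-28 call, as a new episode.

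The cost is SAP wording and modest programming. Items 1 and 2 need nothing beyond daily follow-up and discharge dates. Item 3 has a real downside: the protocol does not say that the call records the cause, date or SOFA of a readmission, so that analysis uses a looser event definition and should be labelled accordingly.
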